### **12.3 RECORDING TYPICAL COMPLICATIONS OF PREMATURITY**

The secondary outcome criteria include the typical complications of preterm birth. These include:

- Incidence of respiratory distress syndrome requiring:
  - Respiratory support (CPAP, positive pressure ventilation, non-invasive high frequency ventilation, invasive pressure ventilation, invasive high frequency ventilation).
  - Administration of intratracheal surfactant (invasive and less-invasive).
- Pneumothorax
- Pneumoperitoneum

- Incidence of IVH °I - °IV according to the criteria of Papile et al (16).
- Incidence of periventricular leukomalacia (PVL) and/or porencephaly
- Incidence of NEC (surgical or conservative treatment)
- Incidence of SIP (surgical or conservative treatment)
- Incidence of ROP requiring treatment
- Incidence of BPD, based on criteria defined by Walsh et al (17)
- Incidence of hyperviscosity syndrome caused by polyglobulia with impaired organ perfusion, defined as follows:
  - Polyglobulia characterized by a centrifuged hematocrit >65% or an Hb >22 g/dL in a peripheral venous blood draw and (at least one of the following points apply):
    - FiO2 requirement >0.3 for more than 12 hours without the presence of other causes such as: respiratory distress syndrome, pulmonary hypertension, vitium cordis, pneumothorax, infection.
    - Lactatemia of >3.0 mmol/l from peripheral venous or arterial blood gas analysis without presence of other causes such as: Vitium cordis, hemodynamically relevant persistent ductus arteriosus, metabolic disease, infection, acute hemorrhage, IVH
    - Reduced diuresis of < 0.5 ml/kg body weight per hour without the presence of other causes including: Infection, persistent ductus arteriosus, drug therapy with indomethacin or ibuprofen.

## 12.4 CRITERIA FOR PREMATURE TERMINATION OF THE STUDY

The principal investigator may decide to stop the study before its completion. The principal investigator will discuss the termination of the study with the Steering Committee.

In this context, the following complications have to be considered with special attention:

1. Clinical compromise due to hyperviscosity syndrome in terms of impaired organ perfusion (see Section 12.3)
2. severe neonatal hyperbilirubinemia requiring treatment (defined by the number of exchange transfusions)
3. Infant death prior to discharge from hospital
4. Maternal death prior to discharge from hospital.

A summary, of the criteria described above for both study arms will be provided every 3 months and presented to the Steering Committee with an external expert.

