### **7.3 FEASIBILITY**

Another aim of the study is to investigate the feasibility of EPT.

According to conservative estimates, in 10-20% of elective cesarean deliveries it is not possible to deliver the placenta together with the infant. Possible reasons for this are, for example, a deep position of the placenta, adhesions and a possible maternal blood loss. In addition, the feasibility of EPT after birth of the infant in the context of neonatal resuscitation will be investigated.

Therefore, another aim of the study is to evaluate the frequency with which EPT is not feasible and to detect possible influencing factors.

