#### 10.2.1.6 PROCEDURE IF INTERVENTION IS NOT PERFORMED

If, despite allocation of the infant to the intervention group, the development of the placenta by obstetrics is not possible (e.g. deep placental position) or if there are concerns by the obstetrics (long duration of development, maternal complications such as severe blood loss, etc.), it is up to obstetrics to stop the intervention in this situation and, if necessary, to immediately clamp the cord (ICC) or perform umbilical cord milking (CM). In this case, the further procedure of neonatal resuscitation is

based on the procedure of the control group. Nevertheless, the collection of primary and secondary target criteria is performed. (intention-to-treat principle).

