### **12.2 RISKS AND EXPOSURES ASSOCIATED WITH STUDY PARTICIPATION**

On the other hand, no relevant risks are known from clinical experience and previous retrospective studies. Theoretically, however, it is possible that EPT may cause polyglobulia resulting in hyperviscosity due to the transfusion of umbilical cord blood. Because of the increased accumulation of hemoglobin, there could be subsequent aggravation of neonatal hyperbilirubinemia. However, there was no evidence for this in the retrospective data analysis from 2015 (8).

Since the collection of the additional blood samples required as part of the study is performed only as part of necessary routine blood sampling, additional stress, pain, and irritation to the infant are minimized.

The sample volume required from the blood collection on day 28 of life is 500µl (0.5ml). According to EMEA recommendations, a single study-related blood sample in premature and newborn infants should not exceed 1% of the infant blood volume, and in the case of multiple blood samples, should not exceed 3% of the infant blood volume cumulatively (22). Based on an infant blood volume of 80 (-100) ml/kg, the first benchmark of 1% would be met by drawing 500µl of blood from an infant body weight of at least 625g ( $0.625\text{kg} \times 80\text{ml} = 50\text{ml}$  blood volume.  $0.5\text{ml} / 50\text{ml} = 1\%$ ). The smallest patients included in the study will be the equivalent of 28 weeks' gestation at the time of blood collection. At this time, the mean body weight is approximately 1000g (23). The collection of 500µl of blood therefore amounts to approximately 0.6% of the infant blood volume, thus no relevant impact of the blood collection on the infants can be assumed.

Overall, we therefore conclude that the risk-benefit ratio is positive.

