#### 14.4.7 TARGET MATERNAL VARIABLES

- Blood loss during labour (in ml).
- Minimal Hb level in 24 hours after delivery (in g/dl)
- Survival until discharge from hospital ("yes" or "no")
- Duration of hospitalization (in days)

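### The 3-monthly safety summary by arm has death as its only maternal item, although the protocol names maternal blood loss as a reason EPT fails or is stopped and already collects it

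*Protocol*

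**What the plan says.** Section 12.4 lets the principal investigator stop the study early after discussion with the Steering Committee, and lists four complications that deserve particular attention: hyperviscosity syndrome with impaired organ perfusion, severe hyperbilirubinemia counted by exchange transfusions, infant death before discharge, and "Maternal death prior to discharge from hospital". The scheduled report is tied to that list: "A summary, of the criteria described above for both study arms will be provided every 3 months and presented to the Steering Committee", together with an external expert.

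Elsewhere the protocol treats maternal bleeding as a foreseeable event when the placenta is delivered with the infant:

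- Section 7.3, on why joint delivery may not be possible: "a deep position of the placenta, adhesions and a possible maternal blood loss".
- Section 10.2.1.6, on grounds for obstetrics to stop the intervention: "maternal complications such as severe blood loss".
- Section 14.4.7 collects maternal blood loss in ml, the lowest maternal Hb in the 24 hours after delivery, survival to discharge and length of stay.

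Section 12.2, on risks, states that "no relevant risks are known from clinical experience and previous retrospective studies". It then discusses polyglobulia, hyperbilirubinemia and blood sampling, all in the infant, and names no risk to the mother.

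**The concern.** EPT changes the mother's operation as well as the infant's care. The placenta is delivered with the infant, in the intact sac or after being detached from the uterus (section 10.2.1.4), whereas in the control arm the cord is clamped after a wait with the infant held at placental level (section 10.2.1.3). A difference in maternal bleeding between arms is therefore a natural safety question, and the protocol shows awareness of it by naming blood loss twice and by measuring it.

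The scheduled review does not use that measurement. For infants, section 12.4 tabulates two non-fatal harms plus death; for mothers, it tabulates death alone. A moderate shift in blood loss between arms is hard to see from individual cases, because each case can look ordinary. It shows when values are set out by arm, which section 12.4 already arranges for the other harms. At stake is whether the committee and its external expert see maternal bleeding data routinely while recruitment is still open.

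**Working it through.** **Step 1. The passages side by side.**

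| Item | Named as a reason EPT fails or is stopped | Collected | In the 3-monthly summary by arm |
|---|---|---|---|
| Maternal blood loss | Yes (7.3, 10.2.1.6) | Yes, in ml (14.4.7) | No |
| Lowest maternal Hb, 24 h | No | Yes (14.4.7) | No |
| Maternal death before discharge | No | Yes (14.4.7) | Yes (12.4) |

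The gap lies in routing. The data exist and the report exists, but one does not feed the other.

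**Step 2. Inputs.** The synopsis gives 60 births in two arms of 30. The unit is the birth, so this means 30 mothers per arm. Section 11 gives a recruitment period of about 12 months. The plan states no figure for maternal safety, so there is none to reproduce. Its sample size of 2 × 29 does reproduce: 29 per arm gives 80.2% power with the stated means and SDs and an unequal-variance t-test at two-sided 5% (the 5% is assumed, from the 95% intervals in section 14.1). The point here does not depend on that figure.

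**Step 3. How informative is maternal death?** The protocol gives no maternal mortality rate, so p is an assumption, shown over a range. The chance of at least one death among n mothers is 1 − (1 − p)^n. With n = 30:

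| Assumed p per delivery | Chance of at least one death among 30 EPT mothers |
|---|---|
| 0.01% | 1 − 0.9999^30 = 0.3% |
| 0.05% | 1 − 0.9995^30 = 1.5% |
| 0.1% | 1 − 0.999^30 = 3.0% |
| 0.5% | 1 − 0.995^30 = 14.0% |

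At rates up to 0.1%, the maternal line of the summary would be zero throughout the trial with a probability of at least 97% in the EPT arm.

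**Step 4. What would the collected variables add?** If recruitment is even, 60 / 12 × 3 = 15 births accrue per review, or about 7 to 8 EPT mothers. Blood loss and lowest Hb are continuous, so each mother with a recorded value contributes to every table. A table at the first review would precede about 60 − 15 = 45 births.

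For severe haemorrhage as a yes/no event, at assumed rates of 10% and 20% the same formula gives at least one event among 8 EPT mothers with probability 57% and 83%, and among 30 with probability 95.8% and 99.9%.

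**Step 5. What they would not add.** The table would support judgement; it would not be a powered test. For a comparison of two proportions with n = 30 per arm at two-sided 5%, power = Φ{[|p1 − p2| − 1.96·√(2p̄(1 − p̄)/n)] / √([p1(1 − p1) + p2(1 − p2)]/n)}, where p̄ is the mean of p1 and p2. With assumed severe haemorrhage rates this gives 19% for 10% against 20%, 49% for 10% against 30%, and 78% for 10% against 40%.

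**The case against.** The strongest reply is that the committee is not cut off from maternal bleeding. The list in section 12.4 is for particular attention and is not worded as exhaustive. The principal investigator may stop the study with no stated limit on grounds, and discusses termination with the committee. The allocation is told to all delivery staff before the caesarean (10.2.1.1), obstetrics can stop EPT in the individual case (10.2.1.6), and the reason for each deviation is recorded (14.4.3). At a single centre a cluster of haemorrhages would be noticed. Sections 5.3 and 5.4, on the Steering Committee and external monitoring, were not in the copy examined, so another reporting route cannot be excluded.

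All of this stands. A reader might infer that the review sees nothing but maternal death, that excess bleeding cannot reach the committee, or that it would surface only at the final analysis. The documents support none of these: the summary has four items, and informal routes are open. What remains is that no tabulation of maternal bleeding by arm is scheduled on the text shown.

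A second reply is that the protocol nowhere says EPT causes more bleeding than delayed cord clamping. Table 1 in section 10.2.1.3 lists maternal haemorrhage as a ground for abandoning delayed clamping too, and section 6.1 says EPT is already used in most caesarean deliveries of such infants at the site. This also stands. It means that a difference between arms is an open question, which is a reason to tabulate both arms. Likewise, the 10% to 20% of deliveries in which section 7.3 expects the placenta not to come with the infant covers all causes and must not be read as a haemorrhage rate.

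Third, section 12.2 reports past experience and is not shown to be false. That is right: it is silent about mothers, and the remedy is to reconcile it with the other sections. Nor is there a good case that the Hb variable is defective because transfusion might mask bleeding: it is a minimum, and blood loss is recorded separately.

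**Conclusion.** The point holds as a cheap improvement to safety reporting. The protocol foresees maternal blood loss when the placenta is delivered with the infant and measures it, yet the scheduled summary by arm contains maternal death alone for the mother. On the text shown, an excess of bleeding in the EPT arm would reach the Steering Committee and external expert only at the principal investigator's discretion.

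The size rests on two things. One is the planned 30 mothers per arm. The other is an assumed mortality of 0.01% to 0.1% per delivery, a range that is not in the protocol; at those rates death is very unlikely to occur at all and so says next to nothing about maternal safety. The routing gap itself does not depend on any assumed rate. It would fall away only if the sections not seen (5.3, 5.4) provide for regular reporting of maternal bleeding by arm.

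**What to change.** In section 12.4, add maternal blood loss (ml) and lowest maternal Hb in the 24 hours after delivery, each by arm, to what is summarised every 3 months for the Steering Committee and external expert. Reconcile section 12.2 with 7.3 and 10.2.1.6, so that the risk section addresses maternal blood loss instead of passing over the mother. Recording maternal red-cell transfusion is optional and the point does not depend on it.

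No stopping threshold and no change to obstetric care is proposed. Both variables are already collected, so the cost is a short amendment and a slightly longer quarterly table. With about 7 to 8 EPT mothers per quarter, early tables will be noisy and should be presented as descriptive.

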### **13 MODIFICATIONS IN THE STUDY PROTOCOL**

There is no provision for amending the testing criteria defined in the study protocol. In exceptional cases, however, changes to the testing criteria are possible. These will only be made after agreement between the study management and the local investigators. Changes in the protocol will be submitted to the Ethics Committee of the Medical Faculty of the University of Cologne.

## **14 STATISTIC**

### **14.1 STATISTICAL AND ANALYTICAL PLAN**

Quantitative target values are described with the number of valid and missing values, mean, standard deviation and percentiles (0, 25, 50, 75, 100 (%)), qualitative target values with absolute (n) and relative (%) frequency. In broad aspects, the statistical analysis is based on a descriptive analysis. P-values are to be interpreted two-sided (exceptions are marked), accordingly two-sided confidence intervals (to the 95% level) are given.

### **14.2 STUDY POPULATION**

The primary analytic dataset is the intention-to-treat (ITT) population. This includes all randomized patients evaluated according to their assigned intervention. Only participants subsequently excluded according to section 9.5 are excluded. Intercurrent events are irrelevant for this treatment rule strategy (36).

The secondary evaluation dataset is the per-protocol (PP) population. This includes all patients included in the study who were treated and observed in a substantially protocol-compliant setting.

### **14.3 PRIMARY TARGET VARIABLE**

The primary target variable is the mean haematocrit value in the first 24 hours after birth.

The hematocrit value is given as percentage. If there are > 1 measured values per patient, the arithmetic mean is determined. Group comparison is done by covariance analysis (ANCOVA) with fixed effects: baseline, group, gestational age (24+0 - 27 + 6 SSW vs. > 27+6 SSW) and gravidity (singleton vs. multiples). The influence of missing values is considered and explored via multiple substitutions (sensitivity analysis).

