## **8 STUDY OBJECTIVES**

### **8.1 PRIMARY OUTCOME**

The mean hematocrit value from blood samples taken within the first 24 hours of life is defined as the primary outcome.

All hematocrit determinations within the first 24 hours of life collected during routine clinical care are used for averaging, if at least one determination was performed.

The measurement of the primary outcome is performed by the central laboratory of the Institute of Clinical Chemistry at the University Hospital of Cologne within the framework of clinically indicated routine blood sampling. The value is given as a percent. Hematocrit is usually determined at birth, after 12 hours and after 24 hours. For the last value at 24 hours, a time variance of up to  $\pm 2.5$  hours ( $\approx 10\%$ ) is tolerated.

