### **10.2 PROCEDURE IN CONTROL/INTERVENTION GROUP**

The trial consists of 3 periods.

The first period will start shortly before the birth of the infant with a randomized assignment of the infant to the intervention or control group as well as the implementation of EPT immediately after birth

or delayed umbilical cord clamping and extended monitoring of vital parameters during neonatal resuscitation.

The second period comprises the hospital stay and includes the documentation of clinical parameters and blood tests of the infants, as well as of the mothers. This period ends with an individually variable duration at discharge of the infant and the mother.

The third period occurs at a corrected age of  $24 \pm 2$  months and includes the assessment of the BSID III.

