#### **10.2.2.3 EXPERIMENTAL PART**

For the experimental part of the study, analyses of patient blood samples from both study arms will be performed at two time points. For this purpose, blood from the patient's umbilical cord will be collected (0.5 ml) after the patient's cord has been cut, and 0.5 ml of blood will be collected on the patient's 28th day of life ( $\pm 2$  days) as part of a routine blood sampling. After sample collection, this blood is identified with a prepared label giving the patient's randomization ID. The serum will be centrifuged immediately afterwards in the perinatal center and will be stored at  $-20^{\circ}\text{C}$ . Further examinations are performed in the Laboratory of Experimental Pneumology of the Department of Pediatrics and Adolescent Medicine or in the Center for Molecular Medicine Cologne (ZMMK). No additional data will be collected or separate blood samples taken as part of the study.

The serum samples of the patients are delivered to the ZMMK (Laboratory: Comparative Medicine, Head: PD [name]) following the strict cold storage. A quantitative determination of pro-/anti-inflammatory and angiogenic factors is performed by enzyme-linked immunosorbent assay (ELISA). The Bio-Plex multiplex system (Bio-Plex 200®, Bio-Rad Laboratories, Inc., Hercules, CA, USA) is used for this purpose. The frozen samples are defrosted at room temperature and processed in the multiplex system according to the manufacturer's instructions. After measurement, analysis of the raw data is performed using Bio-Plex Manager™ software (Bio-Rad). Based on the median fluorescence intensity, the concentration of cytokines for each sample is calculated by the system and given in pg/ml.

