#### 14.7 SAMPLE CALCULATION

Our hypothesis is that EPT increases the averaged hematocrit value in the first 24 hours after birth by (relative) 10% (primary outcome), ie, according to (10) from 52.1 $\pm$ 6.6% (Table II, DCC only) to 57.31 $\pm$ 7.26%. To detect this difference with the two-sample t test for unequal variances in two-sided error of 1st kind with a power of 80%, a case number of 2 times 29 evaluable patients, i.e. about 60 patients, is required (Stata 15.1, StataCorp LLC, College Station, TX, USA; power twomeans). By accounting for covariates (baseline, gestational age, gravity) in ANCOVA, the power reduction due to any missing values can be compensated for. Furthermore, the nine twins randomized to EPT will be compared to their control siblings, where the paired t-test still achieves a power of 80% with a one-sided error of 1st kind of 10% and a correlation of 0.5 between the two measurements (power pairedmeans).

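### The primary ANCOVA adjusts for an undefined baseline, and the protocol describes no haematocrit taken before the randomised procedure; if the birth value is used, the EPT estimate is biased toward zero

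*Protocol*

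**What the plan says.** Section 8.1 defines the primary outcome as the mean haematocrit over the first 24 hours: "All hematocrit determinations within the first 24 hours of life collected during routine clinical care are used for averaging". One determination is enough. On timing it says: "Hematocrit is usually determined at birth, after 12 hours and after 24 hours".

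Section 14.3 fixes the primary model: "Group comparison is done by covariance analysis (ANCOVA) with fixed effects: baseline, group, gestational age", with gravidity as the last term. Baseline is therefore a variable separate from group and the two stratification factors. Section 14.7 lists it again and relies on it: "By accounting for covariates (baseline, gestational age, gravity) in ANCOVA, the power reduction due to any missing values can be compensated for". Neither section says what it is.

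On the order of events, section 10.2 has the first period starting "shortly before the birth of the infant with a randomized assignment of the infant to the intervention or control group", with EPT or DCC carried out straight after birth. The only other early sample is for the serum panel in section 10.2.2.3: "blood from the patient's umbilical cord will be collected (0.5 ml) after the patient's cord has been cut".

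**The concern.** In an ANCOVA of haematocrit, a reader would take baseline to mean a haematocrit measured before treatment. The protocol describes none. The earliest is the birth value, which has two faults as a covariate. It is taken after a procedure whose hypothesised effect (section 7.1) is to raise haematocrit, and it is one of the values averaged into the outcome.

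Conditioning on it leaves only the part of the effect that the birth value does not already show. That is not the effect named in section 7.1, which is the influence of EPT on haematocrit over the whole of the first 24 hours. At stake are the size of the trial's single primary estimate and, under some assumptions, most of its power.

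**Working it through.** **1. The plan's own figure.** Inputs from section 14.7: means 52.1 and 57.31 (difference 5.21 points), SDs 6.6 and 7.26, unequal-variance t test, two-sided, 80% power. Alpha is not given there as a number; 0.05 is taken from the 95% confidence level in section 14.1. With 29 per arm:

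- SE = √((6.6² + 7.26²)/29) = √(96.27/29) = 1.82
- noncentrality = 5.21/1.82 = 2.86
- power = 80.2% (28 per arm gives 78.8%)

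The stated 2 × 29 is reproduced, and no covariate enters it.

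**2. Order of events.**

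| Event | Section | Relative to EPT/DCC |
|---|---|---|
| Randomisation | 10.2 | before |
| EPT or DCC | 10.2.1.3, 10.2.1.4 | – |
| Cord sample (serum panel) | 10.2.2.3, 16 | after |
| Haematocrit at birth, 12 h, 24 h | 8.1 | after |

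No haematocrit from before the procedure is described.

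**3. Effect of adjusting for the birth value.** The documents give neither of two quantities needed, so both are assumptions shown over a range: r, the correlation between values within an infant, and f, the effect on the birth value divided by the effect on the 24-hour mean. Assume k values with a common SD and common correlation, and take the SD of the mean as √(96.27/2) = 6.94.

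- Slope of the mean on the birth value: b = [1 + (k − 1)r]/k
- Adjusted effect: 5.21 × (1 − b·f)
- Residual variance: 6.94² × (1 − b), multiplied by 1 + (5.21·f)²/(4σ²), where σ² = 6.94²/b is the variance of a single value

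Example, k = 3, r = 0.5, f = 1: b = 2/3 and the adjusted effect is 5.21 × 1/3 = 1.74. The residual variance is 48.13/3 = 16.04. With σ² = 72.2 the multiplier is 1 + 27.14/288.8 = 1.094, so the effective SD is √17.55 = 4.19. The noncentrality is 1.74/(4.19 × √(2/29)) = 1.58 and power is 34%.

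Remaining effect in points (share removed; power), k = 3, 29 per arm:

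| r | f = 1 | f = 0.75 | f = 0.5 |
|---|---|---|---|
| 0 | 3.47 (33%; 61%) | 3.91 (25%; 72%) | 4.34 (17%; 81%) |
| 0.25 | 2.61 (50%; 48%) | 3.26 (38%; 68%) | 3.91 (25%; 84%) |
| 0.5 | 1.74 (67%; 34%) | 2.61 (50%; 66%) | 3.47 (33%; 89%) |
| 0.7 | 1.04 (80%; 22%) | 2.08 (60%; 68%) | 3.13 (40%; 96%) |
| 0.9 | 0.35 (93%; 10%) | 1.56 (70%; 88%) | 2.78 (47%; nearly 100%) |

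A simulation of 10,000 trials per setting (k = 3, f = 1) gave mean estimates of 2.43, 1.74 and 1.06 points at r = 0.3, 0.5 and 0.7, with power 45%, 33% and 23%. The formula gives 2.43, 1.74 and 1.04, with 46%, 34% and 22%.

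**4. Fewer values.** With k = 2 and f = 1, 50% to 95% of the effect is removed for r from 0 to 0.9. For an infant with a single value, which section 8.1 allows, covariate and outcome are the same number.

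**5. Without the covariate.** With group and the two strata only, the model targets the full 5.21 points. Power is 80.2% with 29 per arm and 81.5% with 30, taking no credit for variance explained by the strata.

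**The case against.** The strongest reply is that the protocol never says baseline is the first haematocrit. Variables fixed before randomisation are recorded, such as sex (14.4.1) and antenatal steroids (14.4.6), and adjusting for one of them would do no harm. An SAP, not at hand here, could name the covariate. This stands as far as it goes: the birth-value reading is an inference. But no such variable is called baseline anywhere, and gestational age and gravidity are listed beside it and so cannot be meant. The protocol itself puts the term in the primary model and leans on it in the sample-size argument. An SAP that named the birth value would confirm the fault.

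The second reply concerns size. A reader might infer that the adjustment removes most of the EPT effect and ruins the power. The documents do not support that without conditions, because r, f and the number of values per infant are not given. With three values, more than half is removed only if f = 1 and r exceeds 0.25, or f = 0.75 and r exceeds 0.5. At f = 0.5 it never reaches half, and power stays at 81% or more because the smaller residual variance outweighs the lost effect. What survives is the bias itself, present for any f above 0.

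Thirdly, a reader might dismiss the compensation sentence in 14.7 altogether. That goes too far. Gestational age and gravidity are fixed before treatment and may legitimately reduce residual variance. Only the baseline part fails; the rest is unquantified.

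**Conclusion.** The point holds in conditional form and should be corrected before the primary analysis. What the document establishes is that the primary model contains an undefined baseline and that no haematocrit from before the procedure is described. If baseline is the birth haematocrit, the model conditions on a post-treatment component of its own outcome, and the estimate is biased toward zero whenever EPT raises that value.

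Over r from 0 to 0.9 with three values, the loss runs from 17% to 93% of the planned 5.21 points, depending mainly on how much of the effect is already present at birth. Confidence is high that the term is unusable as a haematocrit baseline. It is lower on the size of the loss, which rests on assumed r and f, equal SDs and correlations across times, and three values per infant.

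It should not be inferred that the sample size is wrong: 29 per arm is reproduced and does not depend on the covariate.

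**What to change.** - In 14.3, delete baseline from the ANCOVA, or replace it with one named variable fixed before randomisation. Keep group and the two stratification factors.
- In 14.7, remove baseline from the covariate list (or put the same named variable in its place). Drop the claim that baseline adjustment compensates for power lost to missing values, and mark any gain from gestational age and gravidity as unquantified.

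The cost is a change of wording in two sections. No new data are needed and the sample size stays as it is. Entering gestational age in days, which 14.4.1 already records, is an optional choice for precision and not part of this correction.

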## **9 STUDY POPULATION**

### **9.1 INCLUSION CRITERIA**

- Birth weight < 1500 gram ("very low birth weight infant")
- Gestational age at birth >23+6 weeks
- Delivery by cesarean section
- Delivery in the tertiary care perinatal center of the University Hospital Cologne
- Written consent of the legal guardian

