### **9.4 METHODS FOR ASSIGNING PARTICIPANTS TO TREATMENT GROUPS**

Participants will be assigned randomly to study group treatments in a 1:1 ratio according to a blocked sequence of computer-generated, pseudorandom codes. Randomization is provided as a set of opaque numbered letters by the Institute of Medical Statistics and Bioinformatics at the University of Cologne. Randomization will be stratified by:

- Gestational age: 1) 24+0 - 27 + 6 SSW, 2) > 27+6 SSW.
- Type of gravidity: 1) singleton, 2) multiple

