## **10 STUDY PROCEDURE**

### **10.1 SCREENING AND ELIGIBILITY ASSESSMENT**

The informed consent of the parents or legal guardians is obtained prior to birth at the Department of Gynecology and Obstetrics, according to the inclusion and exclusion criteria. Reasons for an expected premature birth are maternal (e.g. pre-eclampsia, HELLP syndrome, cervical insufficiency, amniotic infection) or fetal (e.g. intrauterine growth retardation, pathological CTG) pregnancy complications. For this purpose, pregnant women > 23+6 weeks' gestation and < 32 + 0 post menstruationem, in whom premature delivery of the infant is expected < 32 + 0 gestational age and in whom the estimated birth weight of the infant is < 1500 grams, will be informed about the study as potential study participants.

The infant will only be included in the study if the legal guardians (usually both parents, in the case of a single parent, the sole legal guardian) have given their consent after they have been informed about the nature, significance and scope of the trial in an appropriate and comprehensible way, by a physician of obstetrics and neonatology, both orally and in writing, and at the same time have declared with their consent that they agree with the recording of data that will take place within the framework of the trial. If there is a twin pregnancy, a signed declaration of consent from the legal guardians must be available for each infant.

The parents are informed that they can withdraw their consent at any time without giving reasons and without any disadvantages for their infant or themselves. The original written consent will be kept in the study folder at the study center. A copy of the written information and informed consent will be given to parents and guardians.

Since a large number of the described complications leading to premature birth can occur in acute and also unexpected ways, prenatal informed consent of both guardians is not always possible (e.g. in case of a business trip of the father). In this case, the second guardian (usually the father) is informed as soon as possible after birth. If consent is then refused, the infant will be excluded from the study.

The original of the information for the legal guardians and the written consent form will be kept in a study folder in the study center.

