### **14.4 SECONDARY TARGET VARIABLES**

#### **14.4.1 INFLUENCE FACTORS (INFANT)**

- singleton or multiple pregnancy
- birthweight in gramm
- gestational age in days
- sex

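### The primary ANCOVA could use gestational age in days rather than the two randomisation classes: a cheap, small gain in precision, not an error

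*Protocol*

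**What the plan says.** Section 14.3 fixes the primary model: "Group comparison is done by covariance analysis (ANCOVA) with fixed effects: baseline, group, gestational age" and gravidity. It spells out the age term as two classes, "gestational age (24+0 - 27 + 6 SSW vs. > 27+6 SSW". These are the randomisation strata of section 9.4: "Gestational age: 1) 24+0 - 27 + 6 SSW, 2) > 27+6 SSW".

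Section 14.4.1 lists "gestational age in days" among the infant influence factors, so the finer value is collected anyway.

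Section 14.7 sizes the trial with an unadjusted unequal-variance t test at 29 evaluable infants per arm, about 60 in total. It then argues that, with baseline, gestational age and gravidity in the ANCOVA, "the power reduction due to any missing values can be compensated for". It gives no correlation or explained variance for any of the three.

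**The concern.** The two classes are wide. The inclusion criteria set the lower bound ("Gestational age at birth >23+6 weeks"), and the screening text in section 10.1 addresses women "in whom premature delivery of the infant is expected < 32 + 0 gestational age". Over that window each class spans about 28 days, so an infant of 24+0 weeks is treated like one of 27+6. If haematocrit changes with gestational age inside a class, the class term leaves that variation in the residual.

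At stake is precision only. The plan requires 29 evaluable infants per arm and enrols about 30, and section 14.7 looks to the covariates to absorb losses beyond that. The form in which gestational age enters affects how much it can absorb.

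**Working it through.** **1. The plan's own figure.** Inputs from section 14.7: "from 52.1 $\pm$ 6.6% (Table II, DCC only) to 57.31 $\pm$ 7.26", so the difference is 57.31 − 52.1 = 5.21 with SDs 6.6 and 7.26. The test is two-sided. An alpha of 5% is inferred from the 95% intervals in section 14.1. Power of the unequal-variance t test (Satterthwaite degrees of freedom, noncentral t) is 78.8% at 28 per arm, 80.2% at 29 and 81.6% at 30. The stated 29 per arm is reproduced.

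**2. How much of a linear age effect two classes keep.** Let k be the squared correlation between age in days and the class indicator. The age distribution is not given, so it is assumed over 24+0 to 31+6 weeks:
- uniform: k = 0.75
- truncated normal, SD 2 weeks, mean 28 to 29.7 weeks: k = 0.68 down to 0.59

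**3. Gross effect on variance and power.** Let r be the within-arm correlation of gestational age with mean haematocrit (assumed). Residual variance is proportional to 1 − k·r² with classes and 1 − r² with days. The excess with classes is therefore (1 − k·r²)/(1 − r²) − 1. Power is recomputed at 30 per arm with both SDs multiplied by the square root of the residual share, using k = 0.60 to 0.75 for the classes:

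| r | Excess variance, classes | Power, classes | Power, days |
|---|---|---|---|
| 0.1 | 0.3–0.4% | 81.8–81.9% | 82.0% |
| 0.2 | 1.0–1.7% | 82.5–82.7% | 83.1% |
| 0.3 | 2.5–4.0% | 83.7–84.2% | 85.0% |
| 0.4 | 4.8–7.6% | 85.3–86.2% | 87.7% |
| 0.5 | 8.3–13.3% | 87.3–88.7% | 91.0% |

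**4. In terms of section 14.7.** Scaling 29 by the residual share gives the losses per arm, from 30, that still leave about 80% power.
- r = 0.3, days: 30 − 29 × 0.91 = 3.6. Classes: 30 − 29 × 0.946 = 2.6 to 30 − 29 × 0.9325 = 3.0.
- r = 0.5, days: 30 − 29 × 0.75 = 8.3. Classes: 30 − 29 × 0.85 = 5.4 to 30 − 29 × 0.8125 = 6.4.

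**5. Net effect.** Steps 3 and 4 ignore the cost of estimating an extra term, about 1/53 = 1.9% of variance at 60 infants. Simulating 60 infants with stratified blocks (block size 4 assumed) gives the net change in precision against the planned class term:

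| r | Days replace class | Days added to class |
|---|---|---|
| 0 to 0.1 | within about 1% of zero | about −2% |
| 0.2 | +0.5 to +1% | about −1% |
| 0.3 | +2 to +3% | about 0 to +2% |
| 0.5 | +9 to +10% | about +8% |

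On 60 infants, 0.5% is 0.3 of an infant and 10% is 6.

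**The case against.** The strongest reply is that nothing here is wrong. The classes are the factors used in randomisation, and adjusting for them is the conventional analysis, unbiased and valid. That stands, and it is why the point is offered only as an improvement.

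The second reply is that the gain rests on a correlation the protocol does not supply, and that gross figures flatter it. That also stands. Net of estimation cost, adding days beside the class loses a little precision below about r = 0.3. Variance that gestational age shares with baseline would shrink the gain further; the formulas in steps 3 and 4 do not model this.

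A reader might infer more than the documents support:
- *That the class term conflicts with section 14.7.* It does not. That section says covariates can compensate, names no amount, and does not depend on the form of the age term. With complete data, power with the classes stays above 80% throughout the range examined.
- *That this covariate is the trial's only reserve.* There is also about one spare infant per arm, and the model contains baseline and gravidity.
- *That chance imbalance in age within a class biases the result.* Random imbalance within strata is already reflected in the standard error.

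What survives the reply is narrow. Section 14.3 itself fixes the coarser form, so the choice is not simply left to a later analysis plan. Replacing the class with days uses the same degrees of freedom and costs almost nothing if age proves unrelated to haematocrit.

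**Conclusion.** The point holds as a low-cost efficiency suggestion. The planned analysis is sound, and the sample size of 29 per arm is unaffected because it comes from an unadjusted test. Replacing the two-class term with days gives a net gain of about 0.5 to 10% in precision for r between 0.2 and 0.5, and essentially nothing for r of 0.1 or less. Adding days while keeping the class is worthwhile only from about r = 0.3.

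These figures assume a roughly linear age effect, gestational ages between 24+0 and 31+6 weeks, and the distributions in the working. The upper limit comes from the screening text; section 9.1 sets none. None of the documents' figures shows how strongly gestational age predicts haematocrit within the classes.

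**What to change.** In section 14.3, prespecify before outcome data are seen that gestational age enters the primary ANCOVA as a linear term in days, preferably in place of the two-class term, with group, baseline and gravidity unchanged. Keep the planned two-class model as a sensitivity analysis. If the team prefers to retain every stratification factor in the primary model, add days alongside the class and accept the loss of one degree of freedom, about 2% of variance at 60 infants.

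No new data are needed and the change is one phrase. The small downside is reliance on an approximately linear age effect, which the two-class sensitivity analysis covers.
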